#### Psychometric properties

To examine the psychometric properties of the questionnaires in the Ukrainian language, several analyses will be reported. Exploratory Factor Analyses (EFA) will be conducted using Statistical Package for the Social Sciences (SPSS), Version 26 software. Analysis of the factor dimensional constraints will determine each model’s underlying individual item loadings. Based on the results of the EFA, Confirmatory Factor Analysis (CFA) will then be analyzed. ECA will be used to analyze how to fit the models using several indexes such as Satorra-Bentler χ^2^, CFI, RMSEA and the confidence interval of RMSEA statistics will be calculated. Lagrange multipliers and Wald test will be sequentially performed to improve the models’ fitness, following the study’s hypotheses. Standardized coefficients and measurement equations with scores in R2 will be reported. These analyses will be conducted using the AMOS program.

Prediction models. To examine the risk and protective factors associated with perinatal mental health outcomes, a random sample of 70% of participants will be used to derive the machine learning algorithms, including regularized logistic regression, random forest, decision tree, and gradient boosting to predict the risk of perinatal mental health outcomes, and their performance, and the remaining 30% for validation. First, in the derivation sample, all predictors described above will be included in the models to estimate the probability of depression, anxiety, or PTSD. Beginning with a model containing all potential covariates, the variable with the least significant *p* value will be removed and tested using the likelihood-ratio test until all variables left in the model significantly (at alpha = 0.05) contributed to the model.

In regularized logistic regression models, results will be presented as Odds Ratio (OR) with 95% confidence intervals (CIs).

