Logistic regression analyses will be conducted using the steps forward procedure to examine which variables will predict the study’s dependent variables. This regression analysis makes it possible to predict a dichotomous dependent variable based on predictor, categorical or quantitative variables the R^2^ will be used to calculate the proportion of the explained variance of clinical outcomes by the selected predictors. The different aspects of model performance will be studied. The receiver operating characteristics (ROC) curves (and the corresponding area under the ROC curve—AUC) will also be calculated to test for discrimination characteristics.

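### Backward and then forward stepwise selection, with no rule on which governs, is a poor basis for naming risk and protective factors; conventional intervals would ignore both selection and shrinkage

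*Protocol article*

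**What the plan says.** All of this stands in the protocol article under Data analysis, in the Prediction models paragraph (printed beneath the Psychometric properties heading) and the paragraph after it.

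- Purpose and split: "To examine the risk and protective factors associated with perinatal mental health outcomes, a random sample of 70% of participants will be used to derive" (that is, model derivation), "and the remaining 30% for validation". The algorithms named are regularized logistic regression, random forest, decision tree and gradient boosting.
- Starting model: "all predictors described above will be included in the models to estimate the probability of depression, anxiety, or PTSD".
- First selection, backward: from the full model, the term with the weakest p-value is deleted, each deletion is checked by likelihood ratio, and this repeats "until all variables left in the model significantly (at alpha = 0.05) contributed to the model".
- Reporting: "In regularized logistic regression models, results will be presented as Odds Ratio (OR) with 95% confidence intervals (CIs)".
- Second selection, forward: "Logistic regression analyses will be conducted using the steps forward procedure to examine which variables will predict the study’s dependent variables". No entry criterion is given.
- Performance is then described by R-squared, ROC curves and AUC.

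The article does not say which selection governs, how p-value deletion combines with a penalty, what the penalty is, or how the CIs are computed.

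**The concern.** The second of the main goals listed under Aim is to find which risk and protective factors bear on perinatal mental health. The Conclusion intends the results for policymakers. The reader will therefore use the list of factors, with their odds ratios and CIs, and not only a risk score.

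Two mechanisms distort that list, in opposite directions. Selection at 0.05 keeps a term only when its estimate is far enough from 1 in this sample. Some null terms get through, some true ones are lost, and those kept look too strong. A penalty pulls odds ratios towards 1, and a conventional CI around a shrunken estimate takes no account of that pull. War exposure, the factor the study is about, has no protection against being dropped. With two procedures and no ranking between them, the analyst could also end up with two lists and a free choice.

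**Working it through.** **Inputs.** Minimum sample 300 (Sample size). Derivation 0.70 × 300 = 210 women, validation 90. Alpha 0.05 per term. Prevalences of 14% (anxiety), 25% (depression) and 31% (PTSD) are background figures for migrants in the Introduction, used here as assumptions. The number of model terms is not stated. Table 1 lists seven distinct predictor constructs (one is printed twice), and the study questionnaire has 40 questions. I use 7 to 45 terms; the upper end assumes every question plus five personality traits. The plan gives no figure of its own on this point to reproduce.

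**1. Events.** 210 × 0.14 = 29; 210 × 0.25 = 52; 210 × 0.31 = 65. Per candidate term at 25%: 52/7 = 7.4; 52/20 = 2.6; 52/45 = 1.2.

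**2. False factors.** If all k terms are null and roughly independent, the chance that at least one passes is 1 − 0.95^k. Simulated backward likelihood-ratio elimination (n = 210, 25% prevalence, independent normal predictors) agrees:

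| k | 1 − 0.95^k | Simulated, at least one kept | Mean number kept |
|---|---|---|---|
| 7 | 30% | 32–34% | 0.4 |
| 12 | 46% | 45–50% | 0.7 |
| 20 | 64% | 64–68% | 1.0–1.2 |
| 45 | 90% | 87–90% | 2.9–3.0 |

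The formula contains neither sample size nor prevalence, so recruiting more women does not cure this part.

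**3. True factors lost or inflated.** With five true factors (OR 1.35 per SD) among 20 terms, elimination kept 2.2 to 2.4 of 5, so a given true factor is lost in about half of data sets (1 − 2.4/5 = 52%; 1 − 2.2/5 = 56%). The mean reported OR was 1.61 to 1.64.

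**4. Selection compared with no selection.** Settings: five true factors at OR 1.5, predictor correlation 0.2, n = 210, 300 data sets per row. Entries are mean OR and CI coverage for true factors. Forward entry was set at likelihood-ratio 0.05, which is an assumption.

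| Terms, prevalence | Full model | Backward | Forward | Same set chosen |
|---|---|---|---|---|
| 15, 25% | 1.60, 93% | 1.83, 91% | 1.82, 90% | 89% |
| 20, 25% | 1.61, 94% | 1.84, 92% | 1.84, 92% | 80% |
| 20, 14% | 1.65, 93% | 2.07, 87% | 2.05, 87% | 77% |
| 20, 31% | 1.61, 94% | 1.79, 92% | 1.78, 92% | 83% |

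Part of the inflation (1.5 to about 1.6) is ordinary small-sample bias, present without selection. The rest comes from selection.

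**5. Intervals for false factors.** Among null terms that were kept, only 4–7% of CIs covered OR 1 in these runs, and at most 9% in the others. This is nearly automatic: a term stays because its test rejects OR 1, so its interval excludes 1.

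**6. Penalized intervals.** In the same data sets, ridge regression with Wald-type CIs gave OR 1.40–1.45 and coverage 93–94% under a light penalty, and OR 1.23–1.29 and coverage 55–72% under a heavier one.

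**7. The validation set.** The 90 held-out women test discrimination. With 45 noise terms, apparent AUC was 0.67–0.68 and held-out AUC 0.49–0.50, so validation would show that such a model predicts nothing. It would not say which named factor is false, nor change any OR or CI.

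**The case against.** Several points on the other side stand.

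- **Number of candidates.** A reader might infer that false factors are almost certain. That needs about 45 terms, whereas Table 1 lists seven constructs. With 7 terms the risk is about a third.
- **Events may be more numerous.** The Introduction also cites 34.8% PTSD in displaced pregnant women, and 300 is a minimum without a cap. In a 7-term run with three true factors at OR 1.5, the mean retained OR was 1.66 with 96% coverage at n = 210, and 1.54 at n = 420. Inflation therefore shrinks with more data; false retention does not.
- **Invalid intervals.** A reader might conclude that the planned CIs are simply invalid. The documents do not support that: penalty and CI method are unstated, a light penalty costs almost nothing, and retained true factors were covered in 87–97% of cases.
- **Tree methods.** One might read the elimination as applied to random forest, trees and boosting. The text speaks only of a model with all covariates.
- **Two directions.** Forward selection by p-value is inferred from usual practice. With 20 or fewer terms, backward and forward chose the same set in 77–89% of data sets; with 45 terms, in 61%.
- **Opposing biases.** Inflation applies to unpenalized fits. Regularized odds ratios are pulled towards 1.
- **War exposure** would still appear in the planned bivariate tests, though unadjusted.

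These points limit the size of the problem. They do not supply a governing rule, and they do not make 0.05 selection suitable for naming factors.

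**Conclusion.** The concern holds in a limited form. The article itself fixes two selection procedures for one question without ranking them, and promises odds ratios with CIs from regularized fits. For the risk and protective factor goal, selection at 0.05 gives at least one false factor in roughly one third (7 terms) to 90% (45 terms) of data sets if all candidates are null. It loses about half of true factors of OR 1.35 among 20 terms, and reports those kept at about 1.6 when they are estimated without a penalty. CIs of retained null factors almost never include 1. Loss of coverage from the penalty runs from negligible to large, depending on choices the article does not state.

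These sizes rest on assumed numbers of terms, prevalences, effect sizes and correlations. Prediction is affected less, because the held-out 30% checks it. This should be fixed, but in an exploratory observational survey it is not a defect that stops the study.

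**What to change.** For the second goal, remove both stepwise procedures. Fit one pre-specified, unselected logistic model per outcome, with war exposure, displacement group (in Ukraine or abroad) and the other main predictor constructs of Table 1 always included. Pregnancy outcome can enter only for women who have given birth. Report every OR and 95% CI whatever its p-value. If events are few, use Firth's method with profile-likelihood intervals.

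Keep regularized logistic regression and the tree methods for prediction alone, tuned by cross-validation within the derivation sample and judged on the validation sample, with no p-value elimination and no conventional CIs from penalized fits.

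Suggested wording: *Risk and protective factors will be examined in one logistic model per outcome with a covariate list fixed before analysis; no variable will be removed or added on the basis of its p-value, and all odds ratios with 95% CIs will be reported. Penalized and tree-based models will be used for prediction only.*

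Linear models on the continuous scale scores may be added but are optional. The cost is wording only, with no new data or recruitment. The downside is fewer factors labelled significant and somewhat wider intervals.

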## Introduction

United Nations Population Fund (UNFPA. Ukraine. Conflict compounds the vulnerabilites of women and girls, 2020), estimated that about 265,000 Ukrainian women were pregnant when the war broke out in February 2022. Eighty thousand women were expected to give birth in the subsequent 3 months in Ukraine or abroad (UNFPA. Ukraine. Conflict compounds the vulnerabilites of women and girls, 2020). The current migratory situation in Ukraine varies. The number of women fleeing the country, returning to Ukraine, and remaining in Ukraine even though the ongoing hostilities is difficult to estimate. However, it can be concluded that many Ukrainian women have experienced and will experience stress and/or possible adverse consequences (or trauma) related to the war and forced migration (Ancheva and Morozova, 2016; Zhabchenko et al., 2018; Romanenko, 2020).

To examine and suggest the most effective practices that may reduce the psychological effects of war refugee status on women, members of the “Research Innovation and Sustainable Pan-European Network in Peripartum Depression Disorder—Riseup-PPD” (Cost Action 18138), funded by the European Cooperation in Science and Technology (COST), established the “Perinatal Mental Health and War Refugees status” group.

Even in non-war conditions, the perinatal period (from pregnancy to the first year after the baby is born) is a vulnerable time *per se*. It is estimated that 1 in 5 women will develop a perinatal mental disorder, which implies that the onset and recurrence of mental health disorders during this period is very high (Andersen et al., 2012; Soto-Balbuena et al., 2018, 2021; Fawcett et al., 2019; Legazpi et al., 2022a,b). Depression, posttraumatic stress disorder (PTSD), and anxiety are shown on the literature as the most recurrent diagnoses (Chrzan-Dętkoś et al., 2022). The consequences of war and migration can be particularly damaging for mothers and babies. Studies have shown that the trauma of war or moving to a new area can have long-term negative effects on mental health, leading to an increased risk of depression and post-traumatic stress disorder (PTSD; Hoppen and Morina, 2019; Hoppen et al., 2021).

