### Symptoms

Another objective is to evaluate possible risk and protective factors (including social and economic factors, personality traits, social support, and access to medical/mental health services). We are focusing on the two groups of women who were affected by war during pregnancy: those who left Ukraine and are now refugees in other European countries (known as external refugees) and those who chose to remain in Ukraine (in the same place of residence, considered as internal refugees).

The main goals are the following:To evaluate how perinatal mental health has been affected during the war, by observing the differences in (a) levels of depression, anxiety, post-traumatic stress disorder, and birth trauma; as well as in (b) clinical risk indices (proportion of women above the clinical cut-off point on a validated self-report scale)To research which risk and protective factors have a bearing on perinatal mental health during the war.To examine the links between pregnancy results and mental health of women in war-affected areas.To examine the experiences during the birth and delivery, specifically the potential traumatic events during this period.To assess the perinatal women’s needs concerning support and mental health services in Ukraine and in the host countries.

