### Sample size

No restrictions have been put in place for participant registration. Nevertheless, the sample size was determined by taking into account the number of newborns in Ukraine. Consequently, a minimum sample size of 300 individuals will be recruited using a significance level of α-level of 0.05 and variability of 50%. It is essential to bear in mind, though, that the ongoing war situation, which includes the lack of electricity in Ukraine, the possibility of people evacuating cities, and missiles, may make it challenging to reach this sample size.

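### Every multivariable risk-factor model named in the article has a binary outcome, although goal 2 is not limited to caseness and full-range scores are collected

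*Protocol article*

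**What the plan says.** The goals are listed in the protocol article under the heading Symptoms. Goal 1 separates (a) levels of depression, anxiety, post-traumatic stress and birth trauma from (b) the proportion of women above a clinical cut-off. Goal 2 reads: "To research which risk and protective factors have a bearing on perinatal mental health during the war". It does not mention cut-offs.

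The models for goal 2 are under Data analysis, in the paragraphs on prediction models that follow the psychometric plan. There, "a random sample of 70% of participants will be used to derive the machine learning algorithms", with the remaining 30% for validation. Regularised logistic regression, random forest, decision tree and gradient boosting are used "to estimate the probability of depression, anxiety, or PTSD". A forward logistic regression is then described for the study's dependent variables: "This regression analysis makes it possible to predict a dichotomous dependent variable based on predictor, categorical or quantitative variables". Discrimination is judged by ROC curves and AUC. No linear or ordinal model of a score is named. The Descriptive subsection adds chi-square and Student's t tests, which are bivariate.

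The measures section gives score ranges of 0-30 (EPDS), 0-21 (GAD-7), 0-60 (City BiTS) and 0-88 (IES-R). On numbers, the Sample size section says "No restrictions have been put in place for participant registration" and then "a minimum sample size of 300 individuals will be recruited using a significance level of α-level of 0.05 and variability of 50" per cent. It warns that wartime conditions "may make it challenging to reach this sample size".

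**The concern.** A woman just above a cut-off and a woman at the top of the scale count the same in a binary model, as do a woman just below it and a woman with no symptoms. If the question is which factors move symptoms, that discards information already collected and lowers the chance of finding a real risk or protective factor. The article wants its results to inform policymakers, so a protective factor missed for this reason would matter.

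The cut-offs are a second weakness. The section on translations lists three instruments translated for this study: EPDS, City BiTS and IES-R. A Ukrainian GAD-7 already exists, but the article says its psychometric properties have not been studied. The psychometric work planned is exploratory and confirmatory factor analysis, which does not calibrate a threshold. Several thresholds are listed (EPDS 10 or 13, with 13 called the most useful; GAD-7 5, 10 and 15, with 10 for referral; IES-R 24, 33 and 37), and the modelling text does not say which one defines a case. For City BiTS, a listed outcome, the article gives percentiles and no cut-off, so a binary model of it has no defined outcome.

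**Working it through.** **The plan's own figure.** The stated inputs suggest the precision formula n = z²p(1-p)/e². With z = 1.96 and p = 0.50, a margin e of 5 points gives 385, and 383 with a finite-population correction for 80,000 births, the figure in the Introduction ("Eighty thousand women were expected to give birth in the subsequent 3 months in Ukraine or abroad"). A total of 300 corresponds to e = 1.96 × √(0.25/300) = 5.66 points. No margin is stated, so 300 cannot be reproduced from the text. That is a separate matter. Here 300 is used only as the stated minimum.

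**Information kept after dichotomising.** For a normal score cut so that a proportion p lies above the threshold, and for small effects, the efficiency relative to the continuous score is

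ARE = φ(z_p)² / [p(1-p)],

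where z_p is the normal quantile with upper tail p and φ is the normal density. The values of p below 50% are prevalences cited in the Introduction: 14% generalised anxiety disorder, 25% major depression and 31% PTSD in migrants exposed to armed conflict; 28.2% at high risk of postpartum depression in Syria; 34.8% PTSD in internally displaced pregnant women. They serve here as assumed screen-positive rates.

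| p | φ(z_p) | p(1-p) | ARE | Loss | Effective n of 300 |
|---|---|---|---|---|---|
| 50% | 0.3989 | 0.2500 | 0.637 | 36.3% | 191 |
| 34.8% | 0.3696 | 0.2269 | 0.602 | 39.8% | 181 |
| 31% | 0.3528 | 0.2139 | 0.582 | 41.8% | 175 |
| 28.2% | 0.3378 | 0.2025 | 0.564 | 43.6% | 169 |
| 25% | 0.3178 | 0.1875 | 0.539 | 46.1% | 162 |
| 14% | 0.2226 | 0.1204 | 0.411 | 58.9% | 123 |

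The loss is smallest at p = 50%, so about 36% is a floor under these assumptions.

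**Power for one factor.** Assume a correlation of 0.20 between factor and score, a two-sided 0.05 test and bivariate normality. The approximate power is Φ(0.20 × √(n × ARE) - 1.96), with ARE = 1 for the continuous score.

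- Continuous, n = 300: 0.20 × √300 = 3.46, giving 93%. Simulation (4,000 runs) gives 94%.
- Dichotomised, n = 300: the formula gives 75%, 72% and 60% at p = 31%, 25% and 14%. Simulation gives 77%, 73% and 61%.
- In the 70% derivation sample (0.70 × 300 = 210), simulation gives 83-85% continuous, against 61%, 59% and 46% dichotomised.

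**The case against.** The strongest reply is that binary outcomes suit the stated purpose. The paragraph is about prediction, it sets aside a validation sample, and the Introduction and Discussion speak of identifying women at risk and of screening. Goal 1(b) is itself about cut-offs. This stands: predicting caseness is a legitimate aim, and nothing here shows the binary models to be wrong. It does not cover goal 2, which the same paragraph claims to serve and which is not limited to caseness.

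A second reply is that a condensed article may leave other models to a fuller document. It may, so the point is confined to the models the article names. But the article does state its method for risk and protective factors, and that method is binary throughout.

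Third, the sizes are conditional, and this also stands. A reader might infer that the study will lose 40-60% of its information. The documents do not support that as a fact. The cited prevalences mostly describe disorders in other populations rather than women above these cut-offs, and only the 14% figure takes the loss much beyond 46%. If 40-50% screened positive, the loss would be 36-38%. The published City BiTS percentiles (3, 9 and 18 on a 0-60 scale) suggest skew, so the normal-score figures are least secure there.

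Fourth, continuous models do not make an unvalidated translation valid. True, but they remove the dependence on the threshold.

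**Conclusion.** The point holds for the models named in the article: goal 2 is addressed in multivariable form only through binary outcomes, while four full-range scores are available. The loss is at least about 36%, about 40-46% at screen-positive rates of 25-35%, and about 59% at 14%, given a roughly normal score, small effects and assumed rates.

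The power contrast of about 94% against 61-77% is for a single factor with an assumed correlation of 0.20 in all 300 women. It illustrates the cost and is not the power of the planned multivariable analysis, which selects variables and derives its machine-learning models in 70% of the sample.

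Two further inferences should be avoided. The sample is not fixed at 300: that is a minimum with no cap, though the article doubts that it will be reached. And the GAD-7 was not translated for this study; its weakness is that the existing Ukrainian version is psychometrically unstudied.

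This is an avoidable loss of efficiency with a cheap remedy. It does not invalidate the planned models.

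**What to change.** For goal 2, add adjusted regression of the continuous EPDS, GAD-7, IES-R and City BiTS scores on the same predictor set: linear regression with robust standard errors, or proportional-odds regression where a score is clearly skewed. State that conclusions about which factors matter rest on these models. Keep the logistic and machine-learning models for predicting caseness and for goal 1(b).

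The cost is a few extra models on data already being collected, with no added burden on participants. Linear-model effects will be in score points, so they need a short clinical interpretation beside the odds ratios.

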Mental health professionals who specialize in working with refugees have identified pregnant women and recent mothers as particularly vulnerable members of the migrant community because they are “in a precarious situation in a foreign country, when the sense of inner homelessness can easily develop, and the capacity for empathy and intuitive parenting can be weakened” (Utari-Witt, Walter, 2021, p. 58). For example, a study carried out in war-affected Syria indicated a high percentage (28.2%) of women is at high risk for postpartum depression (Roumieh et al., 2019).

It is also important to note that experiencing war can increase the chances of having a difficult pregnancy and delivery, as well as negative experiences related to childbirth (Fatusic et al., 2005; Arnetz et al., 2013). Along the same lines, exposure to armed conflict can lead to premature birth and babies with low birth weight (Fatusic et al., 2005; Davis and Sandman, 2010; Keasley et al., 2017). However, the likelihood of premature births, stillbirths, and miscarriages increases when there is direct exposure to conflict. For instance, the negative effects often stem from being exposed to a toxic environment with pollutants, radiation, exhaust fumes, or even water or food that has been contaminated in a war zone (Arnetz et al., 2013). Additionally, emerging research has found that women who fled from the Ukraine war experience significant changes in their status, including a loss of a previous lifestyle, daily contact with friends and relatives, financial losses, changes in perinatal health care associated with limited access to health care, and difficulties in finding a health professional (doctor or midwife) that meets all the medical needs (Chrzan-Dętkoś et al., 2022). Additionally, these women report having limited social support (lack of friends, relatives) and live in isolation as a result of being an immigrant (external refugee); research has found that lack of social support (perceived or actual) is a significant risk factor for developing several mental illnesses during the perinatal period (Marcos-Nájera et al., 2020, 2021).

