Another risk factor for mental health is the individual adaptation to a new life in the host country. Heslehurst et al. (2018) reported daily difficulties faced by immigrants and asylum seekers in the host country: not knowing the language and being unfamiliar with the local lifestyle and health practices can create additional burdens and risks for mental and general health. Systematic reviews report that perinatal outcomes such as mental health, maternal mortality, preterm birth and congenital anomalies are predominantly more severe among migrant women (Falah-Hassani et al., 2015: Heslehurst et al., 2018). In a German study, 87.4% of the pre-and postpartum migrants were affected by medical complications or high-risk pregnancies (Kaufmann et al., 2022). However, these studies often do not distinguish among the different statuses of migrant (refugee vs. immigrant) populations, and host countries that may significantly differ regarding the organization of access to support and health care services. For example, an Australian study (Snow et al., 2021) showed elevated psychosocial risk factors among women of refugee background compared with Australia born-women, with the possible under-reporting of mental health problems and family violence. Research on healthcare for pre-, peri- and postpartum refugee women in high-income countries has shown that their access to health care is hampered by immigration experiences, insufficient health literacy, poor language skills, insufficient perception of health needs and use of health services, and legal restrictions (Haith-Cooper and Bradshaw, 2013; Rizkalla et al., 2020). These results raise questions regarding assessing psychosocial risk within different cultural groups and show the importance of the culture-sensitive approach to women with different cultural backgrounds. A systematic review and meta-analysis showed that the prevalence of current PTSD among migrants exposed to armed conflict is 31%, the current major depressive disorder is 25%, and the prevalence of generalized anxiety disorder is 14% (Mesa-Vieira et al., 2022). Migrating to a middle-income or low-income country was associated with an increased prevalence of generalized anxiety disorder—however, evidence is still scarce (Fellmeth et al., 2018).

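### The R-squared of a logistic regression is to be read as the proportion of outcome variance explained, but the versions usual for that model do not measure it, and the protocol names no version

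*Protocol article*

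**What the plan says.** The statement is in the Protocol article, Data analysis, in the prediction-model text that runs on under the heading Psychometric properties. Logistic regression with forward selection is planned to find the variables that predict the dependent variables. On the type of outcome the text says: "This regression analysis makes it possible to predict a dichotomous dependent variable". It continues that the R-squared "will be used to calculate the proportion of the explained variance of clinical outcomes by the selected predictors". No type of R-squared is named there or elsewhere in the article. ROC curves and the AUC "will also be calculated to test for discrimination characteristics". The paragraphs just before describe a random 70% of participants for deriving the models and the remaining 30% for validation, and name depression, anxiety and PTSD as the outcomes. SPSS 26 is named only for the exploratory factor analysis.

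**The concern.** In linear regression, R-squared is the share of outcome variance that the model explains. The usual logistic-regression statistics that carry the same name are built from log-likelihoods and lack this meaning. Cox-Snell cannot reach 1 for a binary outcome, Nagelkerke stretches it so that it can, and McFadden is a relative gain in log-likelihood.

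The article states what its R-squared will be taken to mean, and for these versions that statement is wrong. An analyst who follows the sentence and copies a usual pseudo-R-squared would publish a percentage of variance explained that is something else. Its size would depend on which version was picked. The evaluation of risk and protective factors is one of the study's main goals, and this sentence sets the article's only measure of how much of the outcome those factors explain.

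**Working it through.** The plan gives no R-squared value, so there is no figure to reproduce. The check asks how far each candidate statistic lies from the quantity that the sentence names.

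**Inputs from the document.** The Introduction cites prevalences of 14% (generalized anxiety disorder), 25% (major depression) and 31% (PTSD) in migrants exposed to armed conflict, and 34.8% (PTSD) in internally displaced pregnant women. The Sample size section uses 50% variability. The cited prevalences are background figures, not planning values.

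**Assumptions.** A correctly specified logistic model with one normally distributed linear predictor. Its slope per standard deviation is 0.8 (AUC about 0.70), 1.0 (about 0.74) or 1.2 (about 0.78), and the intercept is solved to match each prevalence. The article gives no expected AUC.

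**Formulas** (p = predicted risk, π = prevalence, l0 and l1 = mean log-likelihood per woman for the null and the fitted model):

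- True explained variance = Var(p) / [π(1 − π)]
- Cox-Snell = 1 − exp[2(l0 − l1)]
- Nagelkerke = Cox-Snell / [1 − exp(2·l0)]
- McFadden = 1 − l1/l0

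**Worked case, π = 0.25, slope 0.8, AUC 0.704.** Var(p) = 0.01918, l0 = −0.56234, l1 = −0.51137.

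- True: 0.01918 / (0.25 × 0.75) = 0.01918 / 0.1875 = 0.102
- Cox-Snell: 1 − exp(2 × (−0.05097)) = 0.097
- Its ceiling: 1 − exp(2 × (−0.56234)) = 0.675
- Nagelkerke: 0.0969 / 0.6752 = 0.144, a ratio to the true value of 1.40
- McFadden: 1 − 0.51137/0.56234 = 0.091

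One model could thus be reported as explaining 9.1%, 9.7% or 14.4% of the variance, when it explains 10.2%.

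**Ratio of Nagelkerke to true explained variance**

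| Prevalence | AUC about 0.70 | AUC about 0.74 | AUC about 0.78 |
|---|---|---|---|
| 14% | 1.60 | 1.54 | 1.48 |
| 25% | 1.40 | 1.38 | 1.35 |
| 31% | 1.36 | 1.34 | 1.33 |
| 34.8% | 1.35 | 1.33 | 1.32 |
| 50% | 1.32 | 1.31 | 1.30 |

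Over the same cells, Cox-Snell divided by the true value runs from 0.82 to 0.99, and McFadden from 0.76 to 1.14.

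**Wider range.** With AUC from 0.58 to 0.93, Nagelkerke overstates by 20% (AUC about 0.92, prevalence 50%) up to 76% (AUC 0.58, prevalence 14%). Cox-Snell runs from 0.68 to 1.00 of the true value, and McFadden from 0.73 to 1.21.

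**Finite-sample check.** In 400 simulated data sets per prevalence, with five predictors and n = 210 (70% of the planned minimum of 300), Nagelkerke divided by the sum-of-squares R-squared was 1.52, 1.38, 1.34 and 1.31 at 14%, 25%, 31% and 50%. This agrees with the large-sample figures.

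**The case against.** The article says only R-squared, and a condensed article may leave the exact version to the full protocol or the SAP. A sum-of-squares (Efron) or Tjur R-squared does estimate explained variance for a binary outcome and would make the sentence correct. This stands, and it limits the point to the likelihood-based versions. It does not remove the point, because the article states an interpretation that is false for the versions usually reported with logistic regression and does nothing to exclude them.

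Three stronger readings are tempting, and the document does not support them.

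- A reader might infer that the reported figure will be too high. That holds for Nagelkerke, which the article never mentions. Cox-Snell understates slightly at moderate discrimination, and McFadden can go either way.
- A reader might infer that R-squared will be computed in the women used to select the predictors. The text does not say which sample is used, and a validation sample exists.
- A reader might object that the figures for anxiety, depression and PTSD could not be compared, because Nagelkerke's inflation grows as the outcome gets rarer. No such comparison is planned. At a fixed slope of 0.8, true explained variance itself moves more with prevalence (0.074 at 14%, 0.116 at 34.8%, a factor of 1.6) than Nagelkerke does (0.119 to 0.156, a factor of 1.3).

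The stakes are also limited. Odds ratios with confidence intervals and the AUC are planned as well, none of them depends on R-squared, and the article does not single out R-squared as the result for policymakers.

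**Conclusion.** The point holds in a limited form. The sentence equates an unnamed logistic-regression R-squared with the proportion of variance explained, which is wrong for Cox-Snell, Nagelkerke and McFadden. If Nagelkerke is used, the overstatement is roughly 30% to 60% in relative terms. In the worked case that is about 4 percentage points (14.4% against 10.2%). This size rests on an assumed AUC of about 0.70 to 0.78, a prevalence of 14% to 50% and a correctly specified model with a normal linear predictor. The upper end depends on the 14% figure, a background prevalence of an anxiety disorder rather than an expected share of women above a scale cut-off. At 50%, the only planning value in the article, the overstatement is 30% to 32%. The consequence is confined to a descriptive measure of model performance.

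**What to change.** Replace the R-squared sentence with wording such as: *Explained variation will be reported as the scaled Brier score (1 minus the Brier score of the model divided by that of a prevalence-only model), computed in the 30% validation sample. Any Cox-Snell, Nagelkerke or McFadden value will be labelled a pseudo-R-squared, with its type named, and will not be interpreted as a percentage of variance explained.*

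A Tjur or sum-of-squares R-squared would serve equally well as the named measure. The scaled Brier score has the practical advantage that it also applies to the planned random forest, decision tree and gradient boosting models.

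The cost is one sentence, a few lines of code and probably a less favourable figure. At the minimum sample of 300 the validation part has 0.30 × 300 = 90 women, or about 22 cases at 25% prevalence (0.25 × 90 = 22.5), so the estimate will be imprecise and should carry a confidence interval. Data collection, tests, odds ratios and sample size are unaffected.
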